## Abstract

**Background:**

Patellar tendinopathy (PT) is a common problem in jumping athletes. Management can be challenging and treatment outcome is not always successful. In combination with tendon loading exercises, hydrolyzed collagen/vitamin C supplementation appears to have a promising effect on the recovery of tendinopathy. The aim of this study is to evaluate whether the use of oral supplementation of hydrolyzed collagen and vitamin C in combination with progressive tendon loading exercises (PTLE) is superior to PTLE and placebo on VISA-P score (which rates pain, function, sports participation) after 24 weeks for athletes with PT.

**Methods:**

The JUMPFOOD study is a double-blinded, two-armed randomized controlled trial, in which the effectiveness of oral supplementation of hydrolyzed collagen/vitamin C combined with PTLE compared to PTLE with placebo on pain and recovery of function in athletes with PT will be investigated. Seventy-six athletes aged 16–40 years, with symptoms of PT for at least 12 weeks, who play sports at least once a week will be included. All participants will receive education, advice with regard to load management and a PTLE program according to the Dutch guidelines for anterior knee pain. In addition, the intervention group will receive daily 10 g hydrolyzed collagen and 40 mg vitamin C supplementation for 24 weeks whereas the control group receives 10 g maltodextrin placebo supplementation. Measurements will take place at baseline and at 12 and 24 weeks’ follow-up. Primary outcome is the VISA-P score, which evaluates pain, function, and sports participation. For secondary outcome measures, data with regard to pain during functional tests, flexibility measurements, blood withdrawals, imaging characteristics of the tendon, and health questionnaires will be collected. During the follow-up period, participants will register sports participation, amount of training and tendon load, pain during sports, co-medication, and side-effects in a digital weekly diary.

**Discussion:**

The JUMPFOOD study is the first large RCT to study the effectiveness of hydrolyzed collagen/vitamin C supplementation in combination with the PTLE program in athletes with patellar tendinopathy. If supplementation of collagen/vitamin C appears to be effective, this treatment can be implemented in daily sports medicine practice to improve the treatment outcome of patients with PT.

**Trial registration:**

ClinicalTrials.gov NCT05407194. Registered on 7 June 2022.

**Supplementary Information:**

The online version contains supplementary material available at 10.1186/s13063-023-07783-2.

## Administrative information

Note: the numbers in curly brackets in this protocol refer to SPIRIT checklist item numbers. The order of the items has been modified to group similar items (see http://www.equator-network.org/reporting-guidelines/spirit-2013-statement-defining-standard-protocol-items-for-clinical-trials/).

## Introduction

### Background and rationale {6a}

Patellar tendinopathy (PT) is a tendon overuse injury that is clinically recognized by load-related pain localized at the inferior patellar pole [1]. Prevalence rates of up to 45% have been reported in elite athletes who participate in sports with repetitive jumping and landing kinetics, such as basketball and volleyball [2]. PT can result in a prolonged absence from sports participation, hampering individuals to achieve their desired performance levels [3]. The pathophysiology and multifactorial etiology of PT have not been elucidated so far; however, (over)load seems to be a driving factor [4]. Education, load management advice, and progressive tendon loading exercises (PTLE) are considered the preferential treatment to improve tendon symptoms, function, and structure [5–7].

Next to the effects of loading on tendon health, nutritional interventions can positively affect collagen synthesis in musculoskeletal tissues [8]. Supplementing 15 g of hydrolyzed collagen in combination with 50 mg vitamin C, 1 h before loading exercises, resulted in an increase in whole-body collagen synthesis and increased mechanics and collagen content of human-engineered ligaments [9]. These data suggest that supplementing hydrolyzed collagen and vitamin C can increase collagen synthesis. This is also hypothesized by Holwerda and Van Loon [10]. They state that mechanical loading as well as dietary intake of glycine and proline (main amino acids present in collagen) could stimulate mRNA transcription and hydroxylation of lysines and prolines, leading eventually to the development of a tropocollagen molecule. The final step, the crosslinking of the tropocollagen into a mature collagen molecule, is thought to be done by ascorbic acid, also known as vitamin C. Based upon this, we hypothesized that collagen and vitamin C in addition to the PTLE program (mechanical loading) might boost the synthesis of collagen, and therefore also the regeneration and recovery of the patella tendon. A recent randomized clinical trial showed that oral supplementation of specific collagen peptides may indeed accelerate the clinical benefits of a well-structured calf-strengthening and return-to-running program in Achilles tendinopathy participants [8]. A case study and explorative prospective phase IV cohort study investigating a similar intervention in athletes with PT also showed promising results [11, 12]. To our knowledge, the effectiveness of oral supplementation of specific collagen peptides in combination with vitamin C and PTLE in athletes with PT has not been studied in a RCT so far. Therefore, the research question of this study is: Is the use of oral supplementation of hydrolyzed collagen/vitamin C in addition to usual care (education, load management advice and PTLE) superior to usual care and placebo on the recovery of PT?

### Objectives {7}

The primary objective of this RCT is to evaluate whether the use of oral supplementation of hydrolyzed collagen/vitamin C in addition to usual care (education, load management advice and PTLE) is superior to usual care and placebo on Victorian Institute of Sports Assessment Patellar Tendinopathy (VISA-P) score (which rates pain, function, sports participation) after 24 weeks for athletes with PT. The secondary objective of this RCT is to evaluate whether the use of oral supplementation of hydrolyzed collagen/vitamin C in addition to usual care is superior to usual care and placebo with regard to other clinical outcome parameters, functional tests, and ultrasonographic tendon structure after 12 and 24 weeks for athletes with PT.

### Trial design {8}

The JUMPFOOD study is a double-blinded, 2-armed randomized-controlled superiority trial (RCT). The duration of the intervention is 24 weeks after inclusion, with an additional follow-up questionnaire at 52 weeks (see Fig. 1A, B). Test days will take place at weeks 0, 12, and 24, with the first test day marking the start of the intervention period. Randomization will be performed as block randomization with a 1:1 allocation. The JUMPFOOD study will take place from February 2023 and is expected to finish at the end of 2025.

**Fig. 1 Fig1:**
[figure not shown]
**A** Timeline of the study with measurements indicated per time point. Abbreviations: VISA-P, Victorian Institute of Sport Assessment—Patella; 3DFR, 3-Day Food Record. **B** Timeline of the test day with measurements indicated per time point. ^1^These blood parameters will only be measured on the first day. ^2^Follow-up questionnaire consists of subjective participant satisfaction with the PTLE program, the return to sports, the pain during activities of daily living, during sports and during the PTLE program, the use of co-interventions, training load, and the compliance of the supplement intake and the PTLE program. The follow-up questionnaire also contains the OSTRC (Oslo Sports Traumatic Research Centre questionnaire) and the SARS (Sports Activity Rating Scale questionnaire). ^3^The ultrasound (grayscale and power Doppler) will be performed at baseline and at 24 weeks. Abbreviations: ESR, (erythrocyte) sedimentation rate; CRP, C-reactive protein; CSI, Central Sensitisation Inventory; EQ-5D, EuroQol-5D-5L; FT4, free thyroxine; Hb1Ac, hemoglobin 1AC; MSK, Keele Start Back-Screening Tool; P1NP, procollagen type 1 N-terminal propeptide; TSH, thyroid-stimulating hormone; UTC, ultrasound tissue characterization; VISA-P, Victorian Institute of Sport Assessment—Patella

This study is registered in the National Institutes of Health (NIH) clinical trials registry (www.clinicaltrials.gov) prior to recruitment (NCT05407194). The study design, procedures, and informed consent procedure were approved by the Medical Ethics Committee (METC Oost-Nederland) of the Radboud UMC, the Netherlands (NL79100.091.22). All participants have to provide written informed consent.

## Methods: participants, interventions, and outcomes

### Study setting {9}

The study will be performed and the data will be collected and handled at the Sports Medicine department of the Gelderse Vallei Hospital in Ede, The Netherlands.

### Eligibility criteria {10}

In order to participate in this study, a participant must meet all of the following criteria: a clinical diagnosis of patellar tendinopathy based on a history of focal knee pain in patellar tendon or its patellar or tibial insertion in association with training and/or competition, palpation tenderness to the corresponding painful area (on the patellar tendon), and/or focal patellar tendon pain during patellar tendon loading with a pain provocation test (single leg decline squat and/or single leg jump squat, NB: imaging findings collected in this project will not be used as an eligibility criterion). Additional criteria are as follows: age 16–40 years old (the chosen age range will minimize chances of other conditions causing anterior knee pain such as osteoarthritis and osteochondrotic diseases like Sinding-Larsen-Johansson syndrome and Osgood-Schlatter disease), a current symptom duration of at least 12 weeks, sports participation at least once a week for at least 1 year before start of complaints, a VISA-P score < 80 out of 100 points, willingness to take (non-vegetarian) nutritional supplements, and willing and able to perform the PTLE program.

Athletes will be excluded if they have a known presence of inflammatory joint diseases (e.g., spondylarthropathy, gout, or rheumatoid arthritis) or familial hypercholesterolemia, if they underwent patellar tendon surgery, if they had a previous patellar tendon rupture of the index knee, if they suffer from acute knee injuries, including patellar tendon injuries with an acute onset, or if they show signs or symptoms of other coexisting knee pathology on physical examination (such as patellofemoral pain syndrome, joint effusion, and joint line tenderness), or if previously performed diagnostic imaging before the start of the study already showed other knee pathology (e.g., chondral lesion of the patella or trochlea on MRI or prepatellar bursitis on US). Athletes who use drugs with a putative effect on the patellar tendon in the preceding year (e.g., fluoroquinolones and statins); athletes who underwent local injection therapy with corticosteroids, other drugs, blood, platelet-rich plasma, or stem cells in the preceding 12 months; athletes who already participate in other concomitant treatment programs or research projects; athletes giving blood donation in a period of 2 months prior to each test day; athletes being pregnant or wish to become pregnant in the upcoming year; athletes who abuse hard drugs; athletes with an alcohol consumption > 21 units/week (men) or > 14 units/week (women); and athletes who already use hydrolyzed collagen supplementation will also be excluded.

### Who will take informed consent? {26a}

The executive researcher will take informed consent. Information about patellar tendinopathy and the purposes and procedures of the study will be presented on a specifically designed website. Athletes with knee pain who are informed about the study will be contacted with regard to possible questions they might have before signing informed consent. After both the participant and the executive researcher have signed the consent, the participant will be asked to fill out an online questionnaire for an in- and exclusion criteria check. After digital screening, those who meet the inclusion criteria will be invited for a clinical screening examination by an experienced sports physician.

### Additional consent provisions for collection and use of participant data and biological specimens {26b}

Additional blood samples will be obtained to be stored for use in future studies evaluating the pathobiology of PT. Information on the usage of blood samples is included in the current informed consent in order to specifically address the collection of these serum and plasma samples.

### Interventions

#### Explanation for the choice of comparators {6b}

All participants will receive education and advice with regard to load management and criteria-based PTLE. The latter consists of 4 stages within the limits of pain according to the multidisciplinary Dutch guidelines for anterior knee pain [13] and, thus, is part of the usual care. PTLE has recently been proven to be superior to eccentric training [6]. Participants will follow this PTLE program until full recovery. This can be sooner than the 24-week intervention. In that case, participants will keep on performing maintenance exercises from the PTLE program.

In addition to the PTLE exercise program, participants will be randomly assigned to receive either the nutritional supplement hydrolyzed collagen/vitamin C (intervention) or a placebo supplement for 24 weeks. Even if full recovery is reached within the 24 weeks of intervention, participants will complete the 24 weeks of supplement usage.

#### Intervention description {11a}

##### Hydrolyzed collagen + vitamin C versus placebo supplement

All participants will receive either a hydrolyzed collagen/vitamin C (intervention) supplement or a placebo supplement. The supplements will be taken per day for a duration of 24 weeks. Each day, the supplement will be taken 1 h before performing exercises from the PTLE program, or, when no exercises have to be performed, in the evening after dinner. The intervention supplement as well as the placebo are both produced by the company Rousselot BV (Ghent, Belgium). The intervention supplement contains 10 g of hydrolyzed collagen, in the form of collagen type I in combination with 40 mg vitamin C (48 kcal). The placebo supplement consists of 10 g maltodextrin (46 kcal). Both intervention and placebo powder are presented as sachets and the powder can be dissolved in cold water. The product is slightly sweetened to mask differences between intervention and placebo supplement.

##### PTLE (progressive tendon loading exercises)

All participants will receive criteria-based PTLE consisting of 4 stages within the limits of pain for 24 weeks. This intervention has recently been proven to be superior to eccentric training [6]. The program has been developed to be performed at the gym or in physical therapy practices. However, it has been modified so that participants can also perform the exercises at home, without equipment. The PTLE will be embedded in the usual care and is a method that is already implemented in many physical therapy practices. The exercise treatment will be explained to the participants by the executive researcher, together with physical therapists who received an explanation about the protocol before the study starts. In addition, the executive researcher will provide written information sheets and will provide a link to video instructions as part of the education. This includes an explanation of the condition, expected management, the positive influence of exercise therapy, and the positive effects of a gradual return to sports. Specific attention will be given to the relation between load and pain using the pain-monitoring model. Modification of all athletic activity (intensity, duration, frequency, and type of load) will be advised for activities that result in considerable patellar tendon pain, namely either significant reduction or even avoidance of the activity. We will stimulate the participants to perform (sports) activities within the limits of acceptable pain (VAS score ≤ 3 points on a scale 0–10, with 0 meaning no pain at all and 10 meaning unbearable pain).

The participants will need to follow an exercise program consisting of isometric (static), isotonic (dynamic), energy-storage (explosive), and sport-specific exercises consecutively, within the limits of acceptable pain [3]. Progression to each subsequent stage is defined using individualized progression criteria, based on the level of pain experienced during a pain provocation test that consists of one single-leg squat. If the VAS-score is 3 or less and exercises of the stage are performed for at least 1 week, progression to the next stage is advised.

Participants are instructed to gradually return to sport-specific training, performed every 2–3 days to allow for recovery from high tendon-loading exercises. In this stage, the isometric exercises of stage 1 will be continued on days that the sport-specific exercises are not performed. When all the exercises in stage 4 are performed within the limits of acceptable pain (VAS score ≤ 3 points), return to competition is recommended. Maintenance exercises are advised when return to play has been achieved. This includes isotonic exercises 3 times weekly and isometric exercises before training or competition.

As mentioned, the first instructions at the start of the intervention period will be given by the executive researcher and a physical therapist. After the elaborate instructions and explanations, participants will follow the exercise program, when possible under the guidance of a physical therapist, as part of their usual care program. Otherwise, the exercise program will be executed at a fitness center or at home. For all situations, instructional videos and an information brochure with explanations and pictures about the exercise program will be provided on a website. During the entire study period, a sports physical therapist with experience in tendon treatment will be available for participants when having questions.

The materials that are needed for home-based completion of these exercises (dynabands) will be offered to the participants after the instruction of the exercise program. The full PTLE program has been published elsewhere and is openly accessible [6].

#### Criteria for discontinuing or modifying allocated interventions {11b}

Participants can withdraw from the study at any time for any reason if they wish to do so without any consequences. The investigator can decide to withdraw a participant from the study for urgent medical reasons.

Since there are no further risks for participants in the study, there are no criteria for withdrawal of the participants based on any risk.

No adverse effects of hydrolyzed collagen or placebo are expected. Hydrolyzed collagen and maltodextrin are generally accepted as safe and have been used in this dosage and marketed in foods and dietary supplements globally for many years. In addition to the supplement, both groups are expected to experience improvement in symptoms as a result of the exercise therapy. In addition, the study has been designed to blend as much as possible with standard clinical care.

#### Strategies to improve adherence to interventions {11c}

Before the start of the intervention, participants will receive an elaborative explanation about the supplement and the exercise program. The explanation is also provided on the website, including short video clips with the exercises and a pdf containing all information about the exercise program.

Two factors will be monitored to keep track of study adherence: (1) compliance to the supplement intake (number of empty and unused supplement sachets brought by the participant and via the weekly questionnaire) and (2) compliance to the exercise program (total percentage of prescribed exercises performed (amount of load and number of series and repetitions will be monitored)). This will be asked on a weekly basis using a short online questionnaire. These questionnaires will be checked on a weekly basis. When the questionnaire is not filled out on the designated day, a reminder will be sent. With no response, a day later, participants will be called to remind them about the questionnaire.

#### Relevant concomitant care permitted or prohibited during the trial {11d}

Pain relieving medication should preferably not be used, but when participants experience pain with a VAS score of 7 or higher, with a duration of at least 24 h, the use of pain medication will be allowed. Preferably, participants should only use paracetamol (acetaminophen) as pain medication. Long-term use of NSAIDs is not allowed. All pain medication should be reported with the type of pain medication, dosage, date of intake, and reason of intake (e.g., knee pain or other causes of pain). No pain medication is allowed the day before and on the day of the tests. Participants have to report all use of co-interventions (patellar strap, inlays, pain medication, or other) in their weekly diary, as the use of pain-relieving therapies is a variable in this study.

#### Provisions for post-trial care {30}

If participants still experience symptoms after completion of the study, we will advise them to contact the general practitioner for a referral to a sports medicine physician.

### Outcomes {12}

#### Primary outcome measure

##### VISA-P questionnaire

The primary outcome measure of the JUMPFOOD study is the change of the validated and disease-specific VISA-P score over 24 weeks, which will be compared between the supplement and placebo groups. This is a short questionnaire specifically designed for athletes with patellar tendinopathy measuring the severity of the injury by assessing pain, function, and ability to participate in sports activities [14]. A VISA-P score of 100 indicates no pain, maximum function, and maximum ability to play sports. The score decreases with increasing severity of symptoms of PT. The VISA-P questionnaire has been translated and validated in Dutch language [14]. The responsiveness of the VISA-P scale has recently been established in athletes with patellar tendinopathy. The minimum clinically important difference (MCID) of the VISA-P score was 13 points in that study [15].

#### Secondary outcome measures

##### Body composition measurements

Body weight (kg), height (cm), and body fat percentage (%) using the sevenfold sum of skinfold will be measured.

##### Blood sampling

At all three test days (*t* = 0, *t* = 12, and *t* = 24 weeks), one blood sample will be drawn at baseline and one will be drawn 1 h after intake of the intervention or placebo supplement. At all test days, a sober blood sample will be drawn for the analysis of BSE and CRP which are general parameters for the determination of inflammation [16, 17]. At only the first test day, uric acid [18–23], cholesterol and lipid concentration [17, 24–28], Hb1Ac [26, 29, 30], thyroid-stimulating hormone (TSH), and free thyroxine (FT4) will be measured, since elevated levels are linked with a higher prevalence of tendon complaints, and thyroid hormones play a role in the etiology of tendinopathy [24, 25, 31].

At all three test days, at baseline and 1 h after intake of the supplement, a blood sample will be drawn to determine the specific N-terminal peptide of pro-collagen I (PINP) concentration change due to supplement intake and change over time to determine collagen build up in the body.

#### Functional tests

##### Functional tests

Functional tests will be performed to determine the pain rating on a visual analogue scale (VAS) and to determine flexibility and strength. First, the participant has to perform a single leg decline squat where the participant performs a single leg squat to 60° of knee flexion on a 25° decline board. This test was designed to preferentially load the patellar tendon [32–35]. We record the VAS pain score after the first squat and after ten single-leg squats on the decline board. Isometric strength of the quadriceps, hamstrings, and abductors will be measured using the MicroFET (ProCare, Groningen, the Netherlands). Muscle length of the quadriceps and the hamstrings will be measured using a plurimeter. Also, a weight-bearing dorsiflexion lunge test will be performed to measure the angle of dorsiflexion using a plurimeter. Using the OptoGait (ProCare, Groningen, the Netherlands), we will measure ground reaction time during a drop jump test, we will measure the ratio between the tendon and muscle strength during a squat jump vs countermovement jump, and we will measure the difference and ratio between the left and right knee during hop tests (single, triple, medial side triple, 90° medial rotation and side hop test). Finally, a drift test will be performed to measure ground area deviation. All functional tests will first be performed on the contralateral side, followed by the affected side. If both sides are affected, the most affected side will be registered as affected side.

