##### Tendon stiffness

Patellar tendon stiffness will be assessed using myotonometric measurements with the MyotonPRO device (Myoton Ltd, Tallinn, Estonia). The measuring method of this device is based on the free oscillation technique. The following steps occur during a single measurement: (1) the device is placed perpendicular to the skin and a constant pre-pressure is applied for compressing the subcutaneous tissue; (2) a brief mechanical impulse is applied causing damped oscillation of the tissue; and (3) the co-oscillation generated in the tissue is recorded by an accelerometer. The myotonometer has good to excellent test–retest reliability and has been established in previous literature [39].

The anatomical landmark for the patellar tendon stiffness assessment will be the most painful spot in the patellar tendon but also 1 cm below the inferior pole of the patella and the midpoint of the patellar tendon. The participants will lie down on a treatment bench with their knees flexed to 90°, measured with a goniometer. In addition to stiffness measurements on the tendon, the stiffness of the rectus femoris muscle will be measured as well, at 1/3 and 2/3 of the muscle, with extended hip and knee. The myotonometric evaluation will be repeated 3 times per location. Only measures that have a coefficient of variation lower than 3% will be considered; otherwise, the measurement will be repeated.

For all imaging techniques and tendon stiffness measurements, the contralateral patellar tendon will also be examined for comparison. Here as well, if both sides are affected, the most affected side will be registered as the affected side.

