## Data collection and management

### Plans for assessment and collection of outcomes {18a}

Each researcher involved in this study will be trained in the study requirements; standardized measurement of height, weight, and fat percentage; how to handle the myotonometer, caliper, UTC, OptoGait, Castor, and questionnaires; how to prepare the supplements; and how to explain everything and guide the participants during study participation.

During study execution, all data that will be obtained will be filled out in Castor with additional checks within a day. On all test days, the painful knee will be marked in the morning, so every researcher knows which leg the affected leg is. Tests are first performed on the unaffected knee and thereafter on the affected knee.

For further information, see the “Outcomes {12} section.”

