The primary study parameter will be the difference between intervention and placebo in the change in VISA-P score (0–100) over time. The primary outcome will first be analyzed with a linear mixed model. When the residuals of the model are not normally distributed, we will use a generalized linear mixed model instead. As independent variables, the treatment (supplement or placebo), time (time points of the measured variable) and time × treatment will be fixed factors, and the participant will be used as a random factor. Adjustments will be made for those baseline variables that are associated with the primary outcome (*p* < 0.10), using a multivariable analysis and a stepwise backward elimination strategy. Examples of potentially associated variables are baseline vitamin C and collagen amino acid intake, baseline P1NP concentrations, compliance to PTLE program, compliance to supplement use, and use of co-medication. Secondary study parameters will be reported quantitatively as well, in the most commonly used way. For the secondary study parameters, we will choose between the generalized linear mixed model and the linear mixed model in the same manner as for the primary outcome. Here, as independent variables, the treatment (supplement or placebo), time (time points of the measured variable), and time × treatment will be fixed factors, and the participant will be used as a random factor. The dependent variable is the secondary study parameter in question (with as important dependent variables/outcome measures: pain during a single leg decline squat, ultrasound imaging abnormalities, UTC findings, and tendon and muscle stiffness). The same stepwise backward elimination strategy will be used as mentioned above. For parameters that are categorical (dichotomous, nominal, or ordinal) a generalized linear mixed model will be used that is applicable for that specific secondary variable (for example a logistic mixed model for dichotomous parameters, and an ordinal mixed model for ordinal parameters). For these parameters, a similar strategy will be applied as described above.

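### The hop-test outcome is defined as left versus right rather than affected versus contralateral, so an effect on the injured leg is diluted if the wording is followed literally

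*Protocol article*

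**What the plan says.** The Functional tests section of the protocol article lists five hop tests (single, triple, medial side triple, 90° medial rotation and side hop) and gives the derived measure: "we will measure the difference and ratio between the left and right knee during hop tests". No other functional measure in that section is defined by left and right.

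Everywhere else the article works by injured side:

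- Functional tests, on test order: "All functional tests will first be performed on the contralateral side, followed by the affected side".
- The same section, on bilateral cases: "If both sides are affected, the most affected side will be registered as affected side".
- Tendon stiffness: "For all imaging techniques and tendon stiffness measurements, the contralateral patellar tendon will also be examined for comparison".
- Section {18a}: "On all test days, the painful knee will be marked in the morning, so every researcher knows which leg the affected leg is".

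For the analysis, section {20a} uses a mixed model with treatment, time and their interaction as fixed factors and the participant as a random factor. On what enters the model it says: "The dependent variable is the secondary study parameter in question". It gives no rule for side or sign. The outcomes it singles out as important are "pain during a single leg decline squat, ultrasound imaging abnormalities, UTC findings, and tendon and muscle stiffness"; hop tests are not among them.

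**The concern.** Nothing in the eligibility criteria restricts the injured side. When a left-affected athlete recovers, left minus right rises; when a right-affected athlete recovers equally, it falls. A left/right measure averaged over an arm therefore mixes changes of opposite sign, and the treatment-by-time term estimates a diluted quantity.

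The secondary objective in section {7} includes superiority on functional tests. A flat hop-test result produced by the definition could be misread as evidence that the supplement does nothing for function. The wording also leaves the analyst a choice between a signed, an unsigned and an oriented version, which is better settled before the data are seen.

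**Working it through.** **Inputs.** The article gives no effect, standard deviation or power for the hop tests, so there is no plan figure to reproduce for this outcome. For scale only, the VISA-P inputs of section {14} are borrowed: 13/19 = 0.68 SD and 70/2 = 35 per arm. A two-sided two-sample t-test at 0.05 with these inputs needs 34.5, rounded up to 35 per arm, which matches the stated 70; its power is 0.81. Applying 0.68 SD to the hop tests is an assumption. So is a baseline deficit of 1 SD in the affected leg. The share p with the left knee affected is not in the documents and is varied.

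**Signed difference.** Let d be the treatment effect on affected minus contralateral. Left minus right has effect +d in left-affected and −d in right-affected participants:

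E = p·d + (1 − p)·(−d) = d(2p − 1).

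- p = 0.4: −0.2d
- p = 0.5: 0
- p = 0.6: 0.2d
- p = 1: d

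For the ratio, a right-affected participant contributes 1/r where a left-affected one contributes r. Since log(1/r) = −log r, the same factor holds exactly for the log ratio and only approximately for the raw ratio.

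**Unsigned difference.** The absolute left-right difference equals the absolute affected-contralateral difference, so p drops out. Taking absolute values folds the distribution at zero, and part of the improvement disappears once a leg approaches or passes symmetry.

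**Oriented difference.** With the registered side as reference the effect is d, whatever p is.

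**Simulation** (35 per arm, 3,000 replicates per row, one follow-up comparison by t-test, effect 0.68 SD, mean deficit 1 SD):

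| p | Signed left − right: effect, power | Absolute difference: effect, power | Affected − contralateral: effect, power |
|---|---|---|---|
| 0.5 | 0.00, 0.05 | 0.33, 0.47 | 0.68, 0.81 |
| 0.6 | 0.14, 0.07 | 0.33, 0.47 | 0.68, 0.80 |
| 0.7 | 0.27, 0.16 | 0.33, 0.46 | 0.69, 0.81 |
| 0.8 | 0.42, 0.33 | 0.33, 0.47 | 0.69, 0.82 |
| 1.0 | 0.68, 0.80 | 0.33, 0.47 | 0.68, 0.80 |

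The signed effects follow (2p − 1) × 0.68 within simulation error: 0.2 × 0.68 = 0.14 at p = 0.6 and 0.6 × 0.68 = 0.41 at p = 0.8. The absolute version keeps 0.33/0.68 = 49% of the effect. The power values belong to this simple comparison and would differ under the planned repeated-measures model. The factor (2p − 1) in the mean does not depend on that choice.

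**Bilateral cases.** If the affected leg improves by a and the other leg by b, the between-leg difference changes by a − b. When both legs are injured and both improve, b is positive and the index understates the gain, however the legs are labelled.

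**The case against.** The strongest reply is that the sentence describes what is measured, not the analysis variable. It names no sign and no numerator. The same section sets the test order by affected side, and section {18a} repeats this: "Tests are first performed on the unaffected knee and thereafter on the affected knee". The injured leg should therefore be known for each hop record, and a sensible analyst could orient the index. Derivation details of this kind often sit in a fuller protocol or analysis plan.

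Much of this stands. A reader might infer that the hop outcomes are bound to show no effect whatever the supplement does, or that at least 80% of any effect is lost. The documents do not support either. Full cancellation needs a signed variable, an analysis that ignores the registered side, and exactly half the participants affected on the left. The 80% figure holds for a signed contrast with p between 0.4 and 0.6, and that range is assumed.

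A reader might also infer that affected-leg performance must replace any symmetry index, or that bilateral cases should be left out of it. The first is a design preference. The second conflicts with the article's rule for registering bilateral cases and with the intention-to-treat analysis of the whole study population in section {20c}.

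What does not stand is that the wording is therefore adequate. The article did not leave the definition open: it stated one, by anatomical side, against its own convention. A ratio needs a numerator, and only left and right are offered. That the data permit re-orientation shows that the correction is easy.

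**Conclusion.** The point holds as a minor correction. Followed literally, the stated definition multiplies an effect on the injured leg by (2p − 1) if signed, with complete cancellation only at p = 0.5. If unsigned, it roughly halves the effect under the assumed 0.68 SD effect and 1 SD deficit. Oriented by the registered side, it costs nothing. The actual loss cannot be fixed from the documents, because they give neither p nor the sign convention.

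The reach is limited. The hop tests are secondary, are not among the outcomes named as important, and played no part in the sample size. The VISA-P analysis is unaffected, and no data would be irrecoverable.

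**What to change.** In the Functional tests section, change the hop-test comparison from left and right to affected and contralateral, for both the difference and the ratio. State the direction (affected minus contralateral; affected divided by contralateral). Use the side registered at baseline throughout, so that the reference leg cannot switch between test days. In bilateral cases use the most affected side, as the section already provides, and keep all randomised participants in the analysis.

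Optionally, report hop performance of the affected leg alongside, because a between-leg index stays attenuated in bilateral cases even after re-orientation.

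The cost is one sentence and a recoding of data already planned for collection, with no new visits or tests. It should be settled before unblinding.
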